## Abstract

**Background:**

There is an increased risk of premature death in people with severe mental illness (SMI). Respiratory disorders and cardiovascular disease are leading causes of increased mortality rates in these patients, and tobacco consumption remains the most preventable risk factor involved. Developing new tools to motivate patients towards cessation of smoking is a high priority. Information on the motivational value of giving the lung age and prevention opportunities is unknown in this high-risk population.

**Methods/design:**

This article describes in detail a protocol developed to evaluate an intensive motivational tool, based on the individual risks of pulmonary damage and prevention opportunities. It is designed as a randomized, 12-month, follow-up, multicenter study. A minimum of 204 smokers will be included, aged 40 years and older, all of whom are patients diagnosed with either schizophrenia or bipolar disorder (BD). Chronic obstructive pulmonary disease (COPD) will be evaluated using spirometry, and the diagnosis will then be validated by a pneumologist and the lung age estimated. Based on this value, a motivational message about prevention will be issued for the intervention group, which will be reinforced by individualized text messages over a period of 3 months.

The efficacy of the method and the pulmonary damage variables will be evaluated: smoking cessation at the end of follow-up will be confirmed by *cooximetry*, and the COPD diagnosis and the severity of the staging for disease will be assessed.

**Discussion:**

In the context of community care, screening and early detection of lung damage could potentially be used, together with mobile technology, in order to produce a prevention message, which may provide patients with SMI with a better chance of quitting smoking.

**Trial registration:**

ClinicalTrials.gov, ID: NCT03583203. Registered on 11 July 2018.

Trial status: recruitment.

## Background

People living with serious mental illness (SMI) reduces life expectancy by up to 20 years [1]. Tobacco consumption, which is almost three times higher in this group than in the general population, is the main preventable risk factor for mortality [2]: half the patients who are unable to quit will die of causes related to smoking [3].

Despite the fact that the comorbidity between SMI and smoking makes it even more difficult to quit [4], there is growing evidence for the safety and short-term efficacy of the available treatments [3, 5, 6]. Possible ways of raising long-term smoking cessation rates in SMI patients include: improving the pre-treatment preparation phase, combining the available treatments and increasing the length of the maintenance phase [7].

Getting a patient ready to change their addictive behavior requires maximum motivation levels. The decision to continue smoking or to try to change this habit depends on a number of factors, including the balance between the perceived benefits and the risks of continued smoking. This balance can be influenced by personalized messages about the health risks they run, which serve as a “motivational trigger” [8]. In the general population, the most common incentive for giving up smoking is linked to concerns about current or future health problems [9]. Much less is known about the factors influencing the decision to quit in people with SMI. People with schizophrenia [10] and bipolar disorder (BD) [11] could have a lower appreciation for the health risks associated with cigarette smoking. Tidey et al. [12] describe how psychiatric smokers—parallel to the rest—who intended to quit, rated the importance of negative health consequences higher than those who did not. Motivation to quit smoking in this population might increase if they are provided with more tailored information on the negative health consequences of smoking [10, 12].

Respiratory diseases, especially chronic obstructive pulmonary disease (COPD) and pneumonia, are the main causes of death in patients with schizophrenia and BD, alongside cardiovascular disease and cancer [2]. Despite the high rates of smoking addiction, a higher-risk consumption (starting younger, higher levels of nicotine dependence and more intense smoking) [13] and the impact this has on mortality rates, the early diagnosis of COPD is not currently catered for in the health care system and studies of the respiratory damage involved are very rare. Even so, in schizophrenia and other non-affective psychoses, the existence of impaired lung function of possible multifactorial origin and the increased likelihood of obstruction [14] have been reported and the risk of delaying the diagnosis has been stressed [14]. The Spanish Consensus Statement on Physical Health in Schizophrenia and BD mentions the possibility of an increased risk of COPD compared with the general population [15, 16], although there is limited information about BD and this is generally inconclusive due to its lack of statistical power [14].

COPD is the most common respiratory pathology in the general population, and smoking is its main cause in the Western countries [17]: it is estimated that half of those who smoke are likely to suffer from COPD. The most important changes in lung function occur in the early stages of the disease, even before the development of COPD [18]. The reduction in forced expiratory volume in 1 s (FEV1), when adjusted for age and level of consumption, is, per se, a high-risk marker of general mortality [19], cardiovascular mortality [20] and lung cancer [21]. The main health care challenge we face here is early diagnosis [22], and quitting smoking is the only step which is capable of slowing down its progress.

Spirometry is a safe, simple, non-invasive and cost-effective technique, and is the gold standard test in the study of pulmonary function and the early diagnosis of COPD [23]. It can be carried out in the primary care setting and there is a general consensus over the criteria for diagnosis and staging [24]; in smokers over 40 years old, it diagnoses between 21 and 25% of COPD in asymptomatic patients [25]. Although initially, when performed in parallel with other biomedical tests, the value of both test and results in increasing motivation in the general population to quit smoking proved inconclusive [26], renewed interest has been shown in this technique following the results of a clinical trial which informed smokers of the calculation of their “lung age” and achieved an increase in the cessation rate [8, 27]. However, to our knowledge, there is no evidence available of how effective this intervention may be in smokers with SMI.

In the general population, a simple recommendation by the physician can influence and increase the chances of giving up smoking in the long term [28]. In populations at higher risk, such as smokers with an SMI, the recommended intervention is the 5 A’s (Ask, Advice, Assess, Assist and Arrange) [7] – however, there is still a need for greater intensity in generating motivation [29]. Currently, mobile technology represents a cost-effective way of promoting health and preventing disease and the information it can convey about health can help to prompt changes in behavior. However, although interventions through text messages (SMS) are capable of generating extra motivation to quit smoking in the general population, so far there is no evidence in more vulnerable populations, including smokers with SMI [30].

The problem of smoking in this population requires new effective strategies to motivate the patient to attempt to quit and aim for the ultimate goal of complete abstinence. Although the impact of respiratory disease on the mortality rates of these patients is clear to see, the possibilities of an early diagnosis of the damage and its influence on motivating the patient to change are more problematic. Given these needs and the lack of evidence, the information based on individual health risks and on creating chances for prevention provides us with an opportunity to assess the situation. It is possible to implement the study of respiratory damage in an environment of community care for mental health, and SMS technology will help to make the message clearer and more forceful.

In a high-risk population, the probability of finding premature lung damage would be higher. Providing information on prevention opportunities will help the patient move forward through the quitting decision. We therefore propose the following objectives:To measure the level of undiagnosed lung damage in smokers with SMITo evaluate the effectiveness of an intensive anti-tobacco intervention, which offers individualized information on lung damage and possibilities of prevention, as a way of helping patients diagnosed with schizophrenia or BD to quit smoking

## Methods/design

### Study design

This is a multicenter, open, randomized and prospective study, with a 12-month follow-up period. Nine Mental Health Centers from the South of Spain, serving both rural and urban populations in the provinces of Córdoba, Jaén, Málaga and Granada, will take part in the study.

The study protocol (version 1: 11/2016) has been approved by the Ethics Committee of Reina Sofía Hospital in Córdoba, Spain, and informed consent will be obtained from each participating patient before recruitment. The http://ClinicalTrials.gov identifier was NCT03583203.

### Recruitment and randomization (see Fig. 1)

This will be a pioneer study in populations with SMI and, for this reason, reference figures from similar studies [31] have been used to calculate the sample size, adjusted to the characteristics and severity of the sample. Abstinence after 12 months was estimated at 3 and 15% in the control and experimental branches, respectively. A level of confidence of 95% and a power of 80% is assumed, which requires a minimum of 85 patients per branch, with an added 20% for possible losses during follow-up.

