**Fig. 1 Fig1:**
[figure not shown]
Flow diagram of study design

Recruitment of at least 204 patients who meet all the inclusion criteria and none of exclusion criteria will be carried out over 1 year and follow-up appointments will be arranged after that.

Inclusion criteria: (1) patients aged between 40 and 70 years; (2) confirmed diagnosis of BD or Schizophrenia according to *Diagnostic and Statistical Manual of Mental Disorders, 4th edition, text revision* (DSM-IV-TR); (3) active smokers who currently consume at least 10 CPD, with a cumulative consumption of 10 packets/year or more; (4) have signed an informed consent to participate in the study.

Exclusion criteria: (1) previous respiratory diagnosis of: asthma, cystic fibrosis, tuberculosis, simple chronic bronchitis, restrictive pulmonary disease or bronchiectasis; (2) acute respiratory symptoms; (3) heart disease or advanced oncological processes; (4) existence of a pathology which makes it advisable not to perform spirometry (recent pneumothorax, recent thoracic or abdominal surgery, aortic aneurysm, unstable angulation, retinal detachment, facial hemiparesis or oral/dental problems); (5) patients who, due to their intellectual disability or mental pathology, do not understand or cannot be forced to perform spirometry; (6) clinical instability with results of over 14 points on the Hamilton Depression Rating Scale (HDRS), a Young Mania Rating Scale (YMRS) score of over 6 or a Positive and Negative Syndrome Scale (PANSS) score of over 70.

The randomization will be carried out using the *Redcap* [32] program, as implemented by the Bioinformatics Unit of IMIBIC (the Maimónides Institute of Biomedical Research in Córdoba, Spain). It will be centralized, performed in permuted blocks and stratified by center, age, gender and pathology. The ratio will be 1:1 for each arm. The research staff will have no knowledge of the assignment until the patient signs their informed consent and has been included in the system (which will automatically assign the patient, once included, to a particular arm).

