### Statistical analysis

The statistical analysis will include all the patients randomized to both branches according to an intention-to-treat approach. The main variable for smoking cessation will be analyzed using the chi-square test for qualitative variables, which in this case consist of the differences between the control and intervention groups. The effect size will be expressed as relative risk (RR), absolute risk reduction (ARR) and the number needed to treat (NNT), with the corresponding 95% confidence interval (CI). The secondary variables will require the comparison of the average values of the quantitative variables between groups (level of motivation, consumption of tobacco according to CPD and expired CO) and will be carried out using Student’s *T* test and its respective post-hoc correction tests. The Mann-Whitney *U* test will be used for the non-parametric equivalent. The association between the quantitative variables will be evaluated using bivariate correlation tests, such as Pearson’s linear correlation coefficients (parametric test) or Spearman’s correlation coefficients (non-parametric test). The respiratory variables for the presence of COPD and its staging will require a descriptive analysis and the results will be presented as frequencies and percentages. Logistic regression models will be used for the multivariate analysis. To control any effects in the comparison between groups caused by contact with the addiction treatment network or the neurocognitive evaluation, the variables associated with these events will be collected and the corresponding adjustments made in the analysis.

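### The 20% loss allowance was multiplied on rather than divided out, so 204 patients keep 85 per arm only up to 16.7% loss; the effect on power is small

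*Protocol article*

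**What the plan says.** All of this is in the protocol article. Under Recruitment and randomization, the planning rates are given as "Abstinence after 12 months was estimated at 3 and 15% in the control and experimental branches, respectively". The error rates follow: "A level of confidence of 95% and a power of 80% is assumed". From these the article concludes that the trial "requires a minimum of 85 patients per branch, with an added 20% for possible losses during follow-up".

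The text after Fig. 1 sets the target: "Recruitment of at least 204 patients". The Abstract gives the same number as a minimum. Allocation is equal: "The ratio will be 1:1 for each arm". The target is therefore 102 per arm.

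Under Statistical analysis, the analysis "will include all the patients randomized to both branches according to an intention-to-treat approach", and cessation is compared with a chi-square test. That section gives no rule for counting patients who are lost.

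**The concern.** The article calls 85 per arm a minimum and says that the extra 20% is there to cover losses. A reader will take it that the trial can lose 20% of its patients and still have 85 per arm. Adding 20% to the required number does not achieve this, because the loss applies to the enlarged number: 20% of 102 is more than the 17 patients added to 85.

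What is at stake is whether the stated recruitment floor delivers the stated requirement for the main efficacy comparison, and how much power is lost if it does not.

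**Working it through.** **Inputs, all from the protocol article.** Control rate 3%, experimental rate 15%, 95% confidence, 80% power, 85 per arm, 20% allowance, 204 in total, 1:1 allocation. Sidedness is not stated; I take the test as two-sided.

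**1. Reproduce 85.** Two proportions, normal approximation, unpooled variance:

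n = (1.960 + 0.842)² × (0.03 × 0.97 + 0.15 × 0.85) / (0.15 − 0.03)² = 7.849 × 0.1566 / 0.0144 = 85.4 per arm.

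This matches 85, rounded down. The pooled-variance formula gives 89, and 105 with continuity correction, so neither is the likely source. A one-sided continuity-corrected version gives 86, also close, but the two-sided unpooled formula is the nearer match.

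**2. Reproduce 204.** 85 × 1.2 = 102 per arm; 102 × 2 = 204. Exact match, so the allowance was multiplied on.

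**3. Apply 20% loss to 204.** 204 × 0.8 = 163.2 in total; 102 × 0.8 = 81.6 per arm. This is 3.4 per arm below 85.

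**4. Number needed to keep 85.** 85 / (1 − 0.20) = 106.25, so 107 per arm and 214 in total, 10 more than 204. Check: 107 × 0.8 = 85.6.

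**5. Loss that 204 can absorb.** 1 − 85/102 = 16.7%.

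**6. Power for 3% versus 15%.** Unpooled power = Φ(0.12 / √(0.1566/n) − 1.960). Exact power is by binomial enumeration of the uncorrected chi-square test.

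| Analysed per arm | Unpooled formula | Exact, uncorrected |
|---|---|---|
| 85 | 79.8% | 82.0% |
| 82 | 78.4% | 80.3% |
| 81 | 77.9% | 79.7% |

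The slip costs 79.8 − 78.4 = 1.4 points at 82 per arm on the formula behind the 85. The pooled formula shows a similar drop, from 78.6% to 77.1%.

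**7. If all 102 per arm are analysed.** The answer depends on what 3% and 15% mean.

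- *Assume* that they are rates among completers, that 20% are lost in each arm, and that losses are counted as smokers. The rates become 0.03 × 0.8 = 2.4% and 0.15 × 0.8 = 12%. At 102 per arm, power is 75.9% (pooled), 77.0% (unpooled) or 79.8% (exact, uncorrected).
- *Assume* instead that they are already rates among all randomised patients. Nothing is diluted, and 102 per arm gives 85.5% (pooled) or 89.2% (exact, uncorrected).

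**The case against.** The wording can be read literally: 20% was to be added, and 20% was added. The article does not separately state an expected loss rate of 20%, and 204 is a floor, so recruiting more is already allowed. This lowers the weight of the point but does not remove it. The text ties the addition to follow-up losses, and a floor is the number at which recruitment may stop.

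A stronger objection is that the power hardly changes. That stands. At 82 per arm the exact uncorrected test still reaches 80.3%.

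A reader might infer that 80% power is missed however losses are handled. The documents do not support that. Counting losses as smokers is a convention the article does not state, and if 3% and 15% already refer to everyone randomised, there is no shortfall in power.

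A reader might also quote a larger deficit: about 77% from the pooled formula, or 69.4% from a continuity-corrected test at 82 per arm. Most of that gap comes from the choice of formula, because the same methods give only 78.6% and 71.6% at the full 85. No continuity correction is specified in the article.

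**Conclusion.** The arithmetic slip is real: 204 does not protect the stated minimum of 85 per arm against 20% loss. The shortfall is 3 to 4 patients per arm, or 10 patients in the recruitment total. It costs about 1.4 points of power on the plan's own formula, and exact power of the uncorrected chi-square test remains about 80%.

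This rests on reading the 20% as the loss to be covered, which is the natural reading, and on a two-sided test. Any further loss of power under the all-randomised analysis is conditional on the two assumptions about completer rates and counting losses as smokers, and is not established by the article.

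The point is minor: a stated figure to correct, not a threat to the design.

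**What to change.** Restate the sample-size sentence in one of two ways:

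- say that 204 patients allow for up to 16.7% loss while keeping 85 per arm; or
- keep the 20% and give the power at that loss, about 78% at 82 per arm on the formula that yields 85.

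Either change costs nothing beyond a slightly less favourable statement. If the sponsor prefers to keep both the 85 and the 20%, the matching floor is 214, which is 10 more patients across nine centres and is compatible with a target already worded as a minimum.

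While editing, it would help to add a few words on whether 3% and 15% refer to completers or to all randomised patients, since that decides whether losses affect power in the planned analysis.

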**Fig. 1 Fig1:**
[figure not shown]
Flow diagram of study design

Recruitment of at least 204 patients who meet all the inclusion criteria and none of exclusion criteria will be carried out over 1 year and follow-up appointments will be arranged after that.

Inclusion criteria: (1) patients aged between 40 and 70 years; (2) confirmed diagnosis of BD or Schizophrenia according to *Diagnostic and Statistical Manual of Mental Disorders, 4th edition, text revision* (DSM-IV-TR); (3) active smokers who currently consume at least 10 CPD, with a cumulative consumption of 10 packets/year or more; (4) have signed an informed consent to participate in the study.

Exclusion criteria: (1) previous respiratory diagnosis of: asthma, cystic fibrosis, tuberculosis, simple chronic bronchitis, restrictive pulmonary disease or bronchiectasis; (2) acute respiratory symptoms; (3) heart disease or advanced oncological processes; (4) existence of a pathology which makes it advisable not to perform spirometry (recent pneumothorax, recent thoracic or abdominal surgery, aortic aneurysm, unstable angulation, retinal detachment, facial hemiparesis or oral/dental problems); (5) patients who, due to their intellectual disability or mental pathology, do not understand or cannot be forced to perform spirometry; (6) clinical instability with results of over 14 points on the Hamilton Depression Rating Scale (HDRS), a Young Mania Rating Scale (YMRS) score of over 6 or a Positive and Negative Syndrome Scale (PANSS) score of over 70.

The randomization will be carried out using the *Redcap* [32] program, as implemented by the Bioinformatics Unit of IMIBIC (the Maimónides Institute of Biomedical Research in Córdoba, Spain). It will be centralized, performed in permuted blocks and stratified by center, age, gender and pathology. The ratio will be 1:1 for each arm. The research staff will have no knowledge of the assignment until the patient signs their informed consent and has been included in the system (which will automatically assign the patient, once included, to a particular arm).

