#### Experimental group

This group will go through a spirometry study for a lung age and obstruction degree determination. The anti-smoking intervention will follow the same duration and general structure of the control group. In this case, when talking about the health risks, personalized information about the lung damage and prevention opportunities will be included. It will teach the patients about comparing lung age with chronological age and explain how the formula is calculated and the origin of the damage. After evaluating their COPD, the patients will be informed about its existence and staging. Depending on the damage found, the generation of motivation will focus on different prevention methods. Likewise, after the motivation level is set, the patients will be offered the option of treatment and regular follow-up. The intervention will be strengthened by motivational messages (designed by specialists from our Addiction Network) in an attempt to give continuity to personal message based on MI—half of which are linked to the possibility of preventing respiratory damage—and sent to the patient's mobile phone via SMS during the 3 months after the face-to-face intervention, with a decreasing rate: three messages per week in the first month, and two and one per week in the following months, respectively (see Table 1 for examples of these messages) [35]. Patients without mobile phones will receive a call on their phone to convey the same messages.

**Table 1 Tab1:** Examples of text messages (SMS) sent to patients in the intervention group

Wanting to smoke is temporary, but the damage to your lungs is permanent – Which kind of suffering do you want to choose?	
The pleasure of breathing in deeply and enjoying a beautiful spring morning would be easier with cleaner lungs. How about trying it?	
Did that little run down the street leave you breathless? Ever thought about giving up smoking? Life is much more bearable with clean lungs.	
If your lungs could speak, they’d be really angry at how you are treating them. It’s up to you – you can make your life better.	
Better health and lung capacity, more cash to spend and less smelly clothes. That’s what you gain when you give up smoking. Difficult to imagine giving up? You’re not alone! Come and see us and we’ll plan it together.	

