### Result variables

Lung damage variables2.1Main variable:Presence of COPD (FEV1/forced vital capacity (FVC) < 0.7, confirmed after bronchodilation) and staging (FEV1 > 80% – mild, FEV1 50–80% – moderate, FEV1 30–49% – severe)2.2Secondary variable:Percentage of FEV1 compared with expected level. Calculation of lung age based on the Fletcher and Peto [36] modelEfficiency variables2.1Main variable:Smoking cessation, defined as self-reported abstinence over the previous 7 days, confirmed by *cooximetry* with expired carbon monoxide (CO) < 10 particles per million (ppm)2.2Secondary variables:Increased levels of motivationNumber of attempts to quit and total duration in days of abstinence, as reported by the patientSmoking cessation objectified by cooximetry (< 10 ppm) at scheduled follow-up appointmentsReduction in the number of cigarettes/day (CPD) smoked, as reported by the patient and confirmed by expired CO after 3, 6 and 12 months

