### Data collection and monitoring (see Fig. 2)

Sociodemographic data:Age, gender, educational level, marital status, number of children, employment status, place of residence, home environment (including other members of the household who smoke) and incomeClinical variables:Confirmation of diagnosis. Schizophrenia and BD sections of the Spanish version of the Structured Clinical Interview for DSM-IV Axis I Disorders (SCID-I) [37]Psychiatric disease variables, as reported by the patient and confirmed by their clinical history. Age of onset, illness duration, number of suicide attempts and number of hospital admissions in the last 5 yearsClinical stability will be assessed by the reference psychiatrist at each center and evaluated by the HDRS [38] and YMRS [39] scales for BD and PANSS [40] for schizophreniaAnxiety symptoms of anxiety. Hamilton Anxiety Rating Scale (HARS) [41]Global functioning. Global Activity Assessment Scale (GAAS) [42]Psychopharmacological treatment at study entry and during the studyComorbidity (from medical history). Anthropometric measurements and vital signs (by nurse, following the schedule):Hypertension, diabetes, dyslipidemia, peripheral vascular disease, heart disease and oncological diseaseHeight, weight, Body Mass Index (BMI), abdominal perimeter, oxygen saturation, blood pressure and heart rateSmoking habitHistory of consumption: age of onset, years of consumption and accumulated consumption (number of packs/year)Current consumption and dependency level:Type and brand of tobacco and CPDExpired CO, reported as ppm, measured with an MD Diagnostic CO Check+ cooximeter (concentration range 0–99 ppm, sensitivity 0.1 ppm). The measurements will be obtained between 11.00 a.m. and 01.00 p.m., with a cut-off point for active smokers of 10 ppm, as in previous references [43].Dependence on nicotine, as evaluated by the Fagerström Test for Nicotine Dependence (FTND) [44]: mild (0–3), moderate (4–7) and severe (8–10)History of previous attempts to quit smoking (minimum 24 h trying to quit):Record of the number of attempts lasting more or less than 1 month. Total sum of days of abstinence reportedPrevious specific treatments, adverse reactions or psychopathological decompensationMotivation to quit smoking:Richmond Test [45]: low (0–4), moderate (5–6) and high (7–10)Analogue visual scale from 1 to 10, measuring the patient’s desire to quit smoking and perceived self-capacity [46]Prochaska and DiClemente’s Stages of Change (SOC) [47]Request for referral to specific treatment of Addictions Network:Number of appointmentsTreatment offeredUse of other substancesThe consumption of other substances—such as alcohol, cannabis, cocaine, stimulants, hallucinogens, heroin, methadone, other opiates or inhalants—will be measured using the “Drug Use Table: Individual Substances” section of the Spanish Addiction Severity Index, 6th version (ASI6) [48]We will record the age of the first consumption, years of regular consumption, consumption for 50 or more days in the patient’s life and consumption over the last 30 days. Consumption will also be calculated for caffeine, measured as cups of coffee/day (one cup of coffee = one energy drink = two cups of tea = three cups of soft drinks [49]), and for cannabis, measured as type (resin or leaf), consumption method (joint or vapor inhalation) and number of joints/year (52 weeks × number of joints/week/365 × number of years smoking) [50]. Patients with cocaine or heroin habits will be noted if the substance is inhaledPhysical activityThe amount of physical activity will be calculated through the self-administered International Physical Activity Questionnaire (IPAQ), used in its shortened version [51] and validated in Spanish [52]. The unit to measure energy expenditure is the MET (Metabolic Equivalent of Task), and the total expenditure in METs-minute/week is calculatedNeuropsychological evaluationIn order to evaluate neurocognitive functioning and any possible changes after the intervention, the Digit Span Test will be used in reverse order or backwards (WAIS-III) [53], together with parts A and B of the Trail Making Test [54], which measure verbal working memory, processing speed and executive attention, respectively

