### Respiratory variables

Respiratory symptoms and impact on quality of life [56]Severity of dyspnea, using the Modified British Medical Research Council (mMRC) scale [57]

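### Objective 1 asks for undiagnosed lung damage, but eligibility, listed history variables, outcome and analysis do not separate known COPD from newly found COPD

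*Protocol article*

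**What the plan says.** All references are to the protocol article.

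- **Objective (Background, last paragraph).** The first of two objectives is to "measure the level of undiagnosed lung damage in smokers with" SMI.
- **Eligibility (Recruitment and randomization).** Exclusion criterion 1 is "previous respiratory diagnosis of: asthma, cystic fibrosis, tuberculosis, simple chronic bronchitis, restrictive pulmonary disease or bronchiectasis". Criterion 2 covers acute respiratory symptoms only.
- **History (Data collection and monitoring).** The comorbidities taken from the medical history are hypertension, "diabetes, dyslipidemia, peripheral vascular disease, heart disease and oncological" disease. The medication recorded is psychopharmacological.
- **Other respiratory data (Respiratory variables).** This section gives "Respiratory symptoms and impact on quality of life" and a dyspnoea scale.
- **Outcome (Result variables).** The main lung damage variable is "Presence of COPD (FEV1/forced vital capacity (FVC) < 0.7, confirmed after bronchodilation) and staging".
- **Analysis (Statistical analysis).** "The respiratory variables for the presence of COPD and its staging will require a descriptive analysis", presented as frequencies and percentages.
- **Who is tested (Experimental group).** "This group will go through a spirometry study for a lung age and obstruction degree determination". The control group description does not mention spirometry.

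**The concern.** The word undiagnosed defines the quantity sought under objective 1, and the rationale in the Background and Discussion rests on screening and early detection. A percentage that mixes known and new cases measures the prevalence of COPD in this sample. It does not measure how much disease had been missed.

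Nothing in the stated criteria keeps out a smoker aged 40 to 70 with an existing COPD diagnosis, and none of the listed variables would identify that patient. Such a patient would test positive and enter the percentage like any other. A claim about under-diagnosis, or about what spirometry adds in community mental health care, would then rest on a figure that is too high. Setting it beside the Background's general-population figure for asymptomatic smokers would mislead in the same direction.

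**Working it through.** **Step 1: is there a stated figure to reproduce?** Not for objective 1. The sample size (85 per arm plus 20%: 85 × 1.2 × 2 = 204) is built on abstinence of 3% versus 15%. It serves the cessation objective and has no bearing on this point.

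**Step 2: the sections side by side.**

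| Element | What is needed for undiagnosed COPD | What is written |
|---|---|---|
| Eligibility | Known COPD excluded, or admitted and flagged | Six respiratory diagnoses excluded; COPD not among them |
| Medical history | A prior-COPD item | Six comorbidities, none respiratory |
| Respiratory variables | A prior diagnosis, or a proxy such as inhaler use | Symptoms, quality of life, dyspnoea |
| COPD record (Safety protocol) | Diagnoses made before the study | Diagnoses made in the study |
| Outcome | COPD not known before | Presence of COPD |
| Analysis | Split or restriction by prior diagnosis | Frequencies and percentages |

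No listed variable links the outcome to the objective.

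**Step 3: direction and size.** Let *p* be the proportion of tested patients with COPD on spirometry, and *k* the share of those cases known beforehand. Assume every known case is positive on spirometry.

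- Reported percentage: *p*
- Rate among patients without a prior diagnosis: *p*(1 − *k*) / (1 − *pk*)
- Overstatement: *pk*(1 − *p*) / (1 − *pk*), which is zero when *k* = 0 and positive otherwise

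The document gives neither *p* for this population nor *k*. Its nearest figure concerns spirometry in smokers over 40 in general: "it diagnoses between 21 and 25% of COPD in asymptomatic patients". That is a yield in people without symptoms, so using its midpoint of 23% as a total that includes known cases is an assumption. The values of *k* are assumptions too.

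| *k* (assumed) | Calculation at *p* = 0.23 | Rate without prior diagnosis | Overstatement |
|---|---|---|---|
| 10% | 0.207 / 0.977 | 21.2% | 1.8 points |
| 30% | 0.161 / 0.931 | 17.3% | 5.7 points |

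Across *p* = 21% to 25% and the same *k*, the rate without a prior diagnosis runs from 15.7% to 23.1%.

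**Step 4: compared with sampling error.** The 95% half-width at 23% is 1.96 × √(0.23 × 0.77 / *n*). This is 8.2 points for *n* = 102 (one arm tested) and 5.8 points for *n* = 204 (both arms). The illustrated overstatements lie within these half-widths, but they are systematic: more patients would not remove them, and the interval would not show them.

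**The case against.** The strongest reply is that this is a condensed article. The full protocol, the case report form and both figures are not shown, and a prior-COPD field may exist there. Criterion 1 cannot be applied without looking at each patient's earlier respiratory diagnoses, so the information probably passes through the investigator's hands. This stands as a limit: one cannot say that the trial fails to collect the item. It does not remove the point. The exclusions and comorbidities are itemised, the data collection section goes down to caffeine equivalents, and the outcome and analysis as printed make no use of prior diagnosis.

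A second reply is that the effect may be small. The Background says early diagnosis of COPD is not provided for in this population, and the Discussion says these patients are less likely to consult for physical complaints. Both suggest that few cases are known. That is fair, and it is why no size can be claimed, but without the item nobody could show it.

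Three stronger readings are tempting, and the document does not support them:

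- **The percentage will certainly count known cases as undiagnosed.** That requires known cases to enrol, and their number is unknown. The outcome is also labelled presence of COPD, so the mismatch is with the objective's wording.
- **The error could not be undone.** A prior diagnosis can be looked up in the clinical record, including for patients already enrolled.
- **Known cases dilute the cessation effect.** Allocation is randomised, so such patients are expected to balance between arms. In the experimental arm they would still receive lung age, staging, prevention advice and three months of messages. No figure supports a dilution.

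**Conclusion.** The point holds as a mismatch within objective 1. The objective names undiagnosed lung damage, while the stated eligibility, variables, outcome and analysis deliver total spirometric COPD. If known cases enrol, the reported percentage is too high as an answer to the objective.

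The size cannot be computed from the document. The drop from 23% to about 21% or 17% is an illustration that rests on an assumed total, an assumed known share of 10% to 30%, and all known cases testing positive. It should not be read as an estimate.

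The consequence is confined to a descriptive objective. The randomised cessation comparison, on which the trial is sized, is not biased. The correction is worth making because it is cheap and the first objective is not answered as worded without it.

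**What to change.** 1. Record prior physician-diagnosed COPD from the clinical history at baseline. For patients already enrolled, retrieve it from the clinical record. If the full protocol or case report form already holds the item, a sentence saying so is enough.
2. Define the objective 1 outcome as post-bronchodilator FEV1/FVC below 0.7 among patients with valid spirometry and no prior COPD diagnosis.
3. Report total spirometric COPD separately. Give each percentage with its denominator and a 95% confidence interval.

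No change to eligibility or to the sample size of 204 is needed, and no patient is lost to the trial. The cost is one field and a slightly smaller denominator for objective 1. Under the illustrative assumptions, 0.23 × 0.10 = 2.3% to 0.23 × 0.30 = 6.9% of tested patients would leave it, that is about 2 to 7 of 102, or 5 to 14 of 204.
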